#### **8.7 Unscheduled Visits**

An unscheduled visit is defined as any visit to the investigator site outside of the protocol-specified timepoints due to safety reasons or when a repeated measurement is required (e.g., obvious measurement errors, confirmation of out-of-range results), where the participant is seen by study personnel.

All unscheduled visits and assessments performed during the visits will be recorded in the participant's electronic case report form (eCRF). During any unscheduled visits the investigator

or qualified designee will record any AE and concomitant medications as well as performing any assessments or collecting samples deemed necessary at the discretion of the investigator.

## **8.8 Protocol Deviations**

All deviations from planned study procedures are to be recorded. Protocol deviations will be reviewed as part of the ongoing data cleaning process.

Prospective approval of protocol deviations, also known as protocol waivers or exemptions, are not permitted.

If there are restrictions to the clinical study as a result of the COVID-19 pandemic, it may be necessary to adjust the visit schedule, convert in-person visits to telephone contacts, and postpone study procedures until the next available study visit. All temporary mechanisms utilized, and deviations from planned study procedures in response to COVID-19 are to be documented as being related to COVID-19 and will remain in effect only for the duration of the public health emergency.

## **8.9 Rationale for the Study Design and Selection of Dose**

This current PsA Phase 2 study will be a randomized, parallel-group, double-blind, placebo-controlled study to evaluate the efficacy and safety of 3 dose regimens of sonelokimab in participants with active PsA.

ACR50 response rate at Week 12 compared with baseline will be the primary endpoint in this study. While ACR20 has historically been the primary endpoint in most PsA clinical programs over the past years, there is precedent in more recent studies (e.g., bimekizumab's BE OPTIMAL and BE COMPLETE) to target a higher ACR50 endpoint [Ritchlin C.T. et al., 2020]. This is driven by the established principle that, across inflammatory diseases, patient benefit correlates with higher levels of measured clinical improvement [Houghton K. et al., 2021]. Notably, in PsA, an inflammatory phase during the course of the disease is often followed by a phase with irreversible tissue destruction demanding therapies with an optimal ("as high as possible") anti-inflammatory effect to potentially provide disease-modifying effects [Eyerich K. et al., 2021].

The primary endpoint will be measured at Week 12 and participants randomized to the placebo group will receive placebo dosing until this timepoint.

Studies with other IL-17 agents indicate that improvement in disease activity may be seen after 12 weeks of treatment. For example, in a Phase 2 randomized, double-blind, placebo-controlled study of bimekizumab for treatment of PsA (NCT02969525), after 12 weeks of Q4W administration, significantly more patients in the active treatment groups of bimekizumab achieved an ACR50 response compared with the placebo group: bimekizumab 16 mg (odds ratio [OR] 4.2 [95% CI 1.1 to 15.2]; p = 0.032), bimekizumab 160 mg (8.1 [2.3 to 28.7]; p = 0.0012), and loading dose of bimekizumab 160 mg (9.7 [2.7 to 34.3]; p = 0.0004) [Ritchlin C.T. et al., 2020].

Sonelokimab has not been tested before this clinical study in a population of patients with PsA. This study will evaluate sonelokimab dose regimens within the range shown to be safe and well tolerated in Phase 1 studies and which have demonstrated efficacy in patients with PsO.

In a Phase 1 PsO study of sonelokimab (NCT02156466) in 44 patients with cutaneous PsO, a significant improvement in PASI100 score in all 4 cohorts of subjects who received 30 mg, 60 mg, 120 mg, or 240 mg sonelokimab was observed, compared with the placebo group. All doses were well tolerated. PASI100 response rates between arms indicated a dose-response relationship up to the 120 mg dose. PASI100 rates between the 120 mg (50.0%) and 240 mg (55.6%) arms did not substantially differ and were both significantly higher than placebo (0%).

In a subsequent Phase 2 PsO study of sonelokimab (NCT03384745) in 313 patients with cutaneous PsO, sonelokimab 120 mg demonstrated a greater clinical response (PASI100) at Week 24 compared with sonelokimab 60 mg, with no unexpected safety findings observed.

Based on clinical programs of IL-17 inhibitors in PsO and PsA, it is hypothesized that clinical efficacy (assessed by the proportion of participants achieving ACR response criteria) may be obtained with a lower dose level in PsA as opposed to PsO [Baraliakos X. et al., 2017; McInnes I.B. et al., 2015; Mease P.J. et al., 2017; Ritchlin C.T. et al., 2020]. For example, in a Phase 3 PsA trial (FUTURE 2) in 397 patients, secukinumab 300 mg (PsO optimal dose) achieved 54% ACR20 response at Week 24, which was not substantially different to the 51% ACR20 response rate with secukinumab 150 mg [McInnes I.B. et al., 2015]. The approved dose of secukinumab is 300 mg Q4W for PsO vs 150 mg Q4W for PsA patients (with no prior anti-TNF therapy).

This study will test sonelokimab at 3 dose regimens for the initial 12 weeks: sonelokimab 120 mg Q2W, sonelokimab 60 mg Q2W, and sonelokimab 60 mg Q4W. These doses are expected to enable preliminary efficacy in PsA to be evaluated and to allow evaluation of an induction regime vs no induction regime approach. From Week 12 onward, the ability of sonelokimab Q4W to maintain response in those participants achieving at least a 20% improvement in their baseline tender and swollen joint count will be evaluated.

The study also has an active reference arm of adalimumab treatment, an approved anti-TNF $\alpha$  drug; however, no formal comparison of sonelokimab vs adalimumab is planned. Alongside the placebo arm, the adalimumab reference arm will be used to calibrate this study's patient population as compared to other clinical programs. After Week 12, participants receiving adalimumab not achieving at least a 20% improvement in baseline tender and swollen joint count will switch to sonelokimab 120 mg Q2W. This change in study treatment will allow initial assessment of the response to sonelokimab in anti-TNF $\alpha$  non-responders.

Inclusion and exclusion criteria have been developed to ensure a well-defined population where efficacy can be determined without introducing any unacceptable risks or confounding effects. The study design incorporates frequent visits and evaluations to optimize assessment of endpoints and collection of safety data.

## **9 STUDY POPULATION**

### **9.1 Eligibility Criteria**

#### **9.1.1 Inclusion Criteria**

To receive randomized treatment assignment, participants must fulfill the following inclusion criteria at the Screening Visit and prior to the initiation of study treatment, unless another time is specified:

1. Participant is  $\geq 18$  years of age;
2. Participant has a confirmed diagnosis of PsA per the 2006 CASPAR with symptoms for  $\geq 6$  months prior to the Screening Visit (see [Appendix 1](#) in Section 21.1);

*Note:* New X-ray images of hands and/or feet are not required. Results of the most recent X-ray images of hands and/or feet will be captured in the eCRF. If no previous images exist, X-rays may be obtained as part of routine management at the discretion of the investigator.

3. Participant has active disease (defined by a TJC68 of  $\geq 3$  and a SJC66 of  $\geq 3$ );
4. Participant has either current active PsO or a dermatologist confirmed history of PsO;
5. Participant tests negative for rheumatoid factor (RF) at the Screening Visit;
6. Participant tests negative for anti-cyclic citrullinated peptide (CCP) antibodies at the Screening Visit;
7. Participant must be, in the opinion of the investigator, a suitable candidate for treatment with adalimumab per approved local product information. If a chest X-ray or computerized tomography (CT) scan for TB screening is required per local guidance, the X-ray or CT scan must be taken within 3 months prior to the Screening Visit;
8. Participant has had an inadequate response at the Screening Visit (lack of efficacy after  $\geq 12$ -week duration of therapy) to previous or current treatment with  $\geq 1$  non-biologic DMARD at maximally tolerated dose, or participant has an intolerance to or contraindication for DMARDs as defined by the investigator;
9. If the participant is female, she must be of non-childbearing potential or, if of childbearing potential, participant must agree to use highly effective methods of contraception. See [Appendix 2](#) in Section 21.2 for the definition of non-childbearing potential, childbearing potential, and highly effective methods of contraception;
10. Women of childbearing potential (as defined in [Appendix 2](#) in Section 21.2) must have a negative serum human chorionic gonadotropin (hCG) pregnancy test at the Screening Visit and a negative urine pregnancy test at Week 0/Day 1 prior to the first administration of study treatment;

11. If male, participant must be willing to use a condom when sexually active with a partner of childbearing potential (as defined in [Appendix 2](#) in Section 21.2) during the study and for 12 weeks after the last dose of study treatment, unless surgically sterile;
12. Participant is considered reliable and capable of adhering to the protocol, visit schedule, or medication intake according to the judgment of the investigator;
13. Participant is able to understand and provide signed informed consent.

### 9.1.2 Exclusion Criteria

Participants who fulfill any of the following exclusion criteria at the Screening Visit or Day 1/Week 0 prior to the initiation of study treatment, unless another time is specified, must be excluded from receiving randomized treatment:

1. Participant with known hypersensitivity to sonelokimab or any of its excipients;
2. Participant with known hypersensitivity to adalimumab or any of its excipients;
3. Participant who currently uses or plans to use one or more prohibited treatments specified in this protocol. Prohibited treatments and washout periods are provided in Section 10.5;
4. Participant who has previously failed on anti-IL-17 therapy, defined as inadequate clinical response, according to the investigator's judgment, after at least 16 weeks of treatment; or is unsuitable for anti-IL-17 therapy for any other reason according to the investigator's discretion;
5. Participant who has previously failed on anti-TNF $\alpha$  therapy, defined as inadequate clinical response, according to the investigator's judgment, after at least 16 weeks of treatment; or is unsuitable for anti-TNF $\alpha$  therapy for any other reason according to the investigator's discretion;
6. Participant who has had previous exposure to more than 2 biologic agents of any type to treat PsA prior to the Screening Visit, including but not limited to IL-17 inhibitors, IL-23 inhibitors, TNF $\alpha$  inhibitors, etc.

*Note:* The total number of participants with previous use of biologic agents will be capped at 30% of the total participant population.

7. Participant who has a diagnosis of chronic inflammatory conditions other than PsO or PsA, including but not limited to rheumatoid arthritis, sarcoidosis, systemic lupus erythematosus, Crohn's disease, or ulcerative colitis;
8. Participant who has a diagnosis of arthritis mutilans;

9. Participant who has an active infection or history of infections, including any of the following:
- Any infection (exception: common cold) requiring systemic treatment within 14 days before initiation of study treatment;
  - Serious infection, defined as infection requiring hospitalization or intravenous anti-infective, within 2 months before initiation of study treatment;
  - History of opportunistic infections caused by uncommon pathogens (e.g., *Pneumocystis jirovecii*, Blastomyces, aspergillus, cryptococcosis), or severe infections caused by common pathogens (e.g., cytomegalovirus, severe herpes zoster e.g. multidermatomal herpes zoster, herpes zoster with organ involvement, ophthalmic herpes, or recurrent herpes zoster [recurrent is defined as 2 episodes within 2 years prior to study treatment initiation]);
  - History of other opportunistic, recurrent, or chronic infections that, in the opinion of the investigator, might cause study participation to be detrimental to the participant;
  - Candida* infection requiring systemic therapy for  $\geq 7$  days in the last 12 months prior to study treatment initiation;
  - Any history of esophageal or systemic candidiasis;
  - Current active candidiasis or *Candida* infection within the last 1 month prior to the Screening Visit;
  - Concurrent acute or chronic viral hepatitis B or C, or human immunodeficiency virus (HIV);
  - Confirmed SARS-CoV-2 infection at the Screening Visit;
- Note:* A participant with an initial positive SARS-CoV-2 result may enter the study provided they are asymptomatic and a negative test (polymerase chain reaction [PCR] or antigen) has been provided prior to study treatment initiation.
10. Participant who received a live (including attenuated) vaccination within 8 weeks before study treatment initiation, or planned to receive a live vaccination during the study and up to at least 12 weeks after the last dose of study treatment. Examples of restricted vaccinations include, but are not limited to:
- Zoster vaccine live (Zostavax);
  - Measles-mumps-rubella or measles-mumps-rubella-varicella;
  - Monovalent live attenuated influenza A (intranasal);
  - Oral polio;
  - Rotavirus;
  - Seasonal trivalent live attenuated influenza (intranasal);

- g. Smallpox;
- h. Oral typhoid;
- i. Varicella (chicken pox);
- j. Yellow fever.

*Note:* See [Appendix 3](#) in Section 21.3 for instructions regarding vaccinations to SARS-CoV-2.

- 11. Participant who received a *Bacillus Calmette-Guérin* (BCG) vaccination within 1 year before study treatment initiation;
- 12. Participant with:
  - a. A history of active TB, i.e., participants having received combination treatment for active TB;
  - b. Evidence of TB infection as defined by a positive QuantiFERON® TB-Gold test (or interferon-gamma release assay [IGRA] equivalent) at screening, unless the following criteria apply:
    - i. A full TB work-up (according to local practice/guidelines) completed within 12 weeks prior to randomization establishes conclusively that the participant has no evidence of active or latent TB;
    - ii. Participants positive for latent TB per work-up must have completed sufficient treatment according to local routine clinical practice at least 4 weeks before randomization.

*Note 1:* If a QuantiFERON TB-Gold test (or IGRA equivalent) at screening is indeterminate, it can be repeated once. The results of the second test are to be used. If the second QuantiFERON TB-Gold test is also indeterminate, the participant should be managed as for participants with positive QuantiFERON TB-Gold test (or IGRA equivalent);

*Note 2:* If there is reasonable medical doubt about a potentially false-positive QuantiFERON TB Gold test (or IGRA equivalent) result, the test can be repeated once after obtaining Medical Monitor approval, and the results of the second test will prevail.

- 13. Participant with any current nontuberculous mycobacterial (NTM) infection or any history of pulmonary NTM infection at the Screening Visit;
- 14. Participant with evidence of acute ocular inflammation, including active anterior uveitis (i.e., acute episode), within the last 4 weeks before study treatment initiation;
- 15. Participant with a concurrent malignancy or a history of malignancy during the past 5 years of the Screening Visit, with the following exceptions:
  - a.  $\leq 3$  excised or ablated basal cell carcinomas of the skin;

- b. One squamous cell carcinoma of the skin not worse than Stage T1 that has been successfully excised or ablated (no other previous treatments allowed), with no signs of recurrence or metastases for at least the past 2 years before study treatment initiation;
  - c. Actinic keratosis;
  - d. Squamous cell carcinoma in situ of the skin successfully excised or ablated at >6 months before study treatment initiation;
  - e. Localized carcinoma in situ of the cervix, treated and considered cured.
16. Participant with fibromyalgia, osteoarthritis symptoms, or any other condition that in the investigator's opinion may potentially interfere with efficacy assessments;
17. Participant with erythrodermic, guttate, or pustular form of PsO or drug-induced PsO;
18. Participant with a history of a lymphoproliferative disorders, including lymphoma, or current signs and symptoms suggestive of lymphoproliferative disease;
19. Participant with primary immunodeficiencies, prior splenectomy, or suppressive conditions, including participants taking immunosuppressive therapy following organ transplants;
20. Participant who had major surgery (including joint surgery) within 6 months before the Screening Visit, or is planning to have major surgery during the study;
21. Participant with the presence of active suicidal ideation, or positive suicidal behavior at the Screening Visit, as evidenced by the C-SSRS assessment that shows any history of suicidal attempt (including an actual attempt, interrupted attempt, or aborted attempt), or suicidal ideation in the past 6 months as indicated by a positive response to either Question 4 or 5 of the C-SSRS at screening;
22. Participant has presence of moderately severe depression or severe depression, indicated by a score of  $\geq 15$  using the screening PHQ-9. Participants are permitted to use 1 medication to treat depression provided dose is stable for 4 weeks prior to initiation of study treatment. Participants on multiple medications for depression are excluded from the study;
23. Participant with severe cardiovascular comorbidities including history of myocardial infarction, unstable angina pectoris, stroke, heart failure (New York Heart Association [NYHA] classification III or IV), or uncontrolled hypertension (characterized by 2 BP measurements separated by at least 15 minutes with systolic BP >160 mmHg or diastolic BP >100 mmHg);
24. Participant with clinically significant ECG abnormalities on centrally read ECG at the Screening Visit;
25. Participant with any other clinically significant medical conditions or any other reason, including any physical, psychological, or psychiatric condition, that in the opinion of the investigator would compromise the safety or interfere with participation in the study, would

make the participant an unsuitable candidate to receive study treatment, or would put the participant at risk;

26. Participant with laboratory abnormalities at the Screening Visit, including any of the following:

- a. Aspartate aminotransferase (AST), alanine aminotransferase (ALT), or alkaline phosphatase  $>3$  times the upper limit of normal (ULN);
- b. Serum direct bilirubin  $>1.5 \times \text{ULN}$  (in the absence of known Gilbert's syndrome);
- c. White blood cell count  $<3.0 \times 10^9/\text{L}$ ;
- d. Absolute neutrophil count  $<1.5 \times 10^9/\text{L}$ ;
- e. Absolute lymphocyte count  $<0.8 \times 10^9/\text{L}$ ;
- f. Platelet count  $<100 \times 10^9/\text{L}$ ;
- g. Hemoglobin  $<85 \text{ g/L}$ ;
- h. Creatinine clearance  $<60 \text{ mL/min}$  (by Cockcroft Gault formula);
- i. Any other laboratory abnormality which, in the opinion of the investigator, might compromise the participant's safety, might prevent the participant from completing the study, or might interfere with the interpretation of the study results.

*Note:* An initial laboratory result obtained at the Screening Visit may be retested one time prior to the initiation of study treatment after consultation with the medical monitor. The result of the second test will then be used.

27. Participant is enrolled in another interventional investigational device or drug study, or has been in another investigational study treatment in the last 28 days prior to the Screening Visit or within 5 half-lives of the other investigational device or study treatment prior to the Screening Visit, whichever is greater;
28. Participant is pregnant or breastfeeding, or plans to become pregnant while enrolled in the study and up to 12 weeks after the last dose of study treatment;
29. Participant has a history of chronic alcohol or drug abuse in the past year prior to the Screening Visit;
30. Participant is an employee, or direct relative of an employee, of the sponsor, at a study site, or of a third-party organization involved in the study.

## 9.2 Screen Failures

Screen failures are defined as participants who consent to participate in the clinical study but are not subsequently assigned randomized study treatment. A minimal set of screen failure information is required to ensure transparent reporting of screen failure participants to meet the Consolidated

Standards of Reporting Trials (CONSORT) publishing requirements and to respond to queries from regulatory authorities. Minimal information includes demography, screen failure details, eligibility criteria, and any SAE.

Clinical laboratories performed at the Screening Visit may be repeated once if they are outside the acceptable range indicated in the exclusion criteria values (Section 9.1). The second value will be used to assess eligibility provided it is received within 28 days of the participant signing the informed consent form (ICF). If the second laboratory value is not received within 28 days of the participant signing the ICF, the participant is considered a screen failure.

Participants who do not fulfill the criteria for participation in this study are not to be re-screened.

### **9.3 Strategies for Recruitment and Retention**

All recruitment material will be approved by an Independent Ethics Committee (IEC) or Institutional Review Board (IRB) prior to implementation.

Regular study monitoring will enable identification of any potential issues related to participant retention.

### **9.4 Study Treatment Discontinuation**

The investigator should discontinue study treatment of a given participant if, on balance, they believe that continuation would be detrimental to the participant's well-being or if the participant plans to initiate any therapies outlined in the prohibited medications list in Section 10.5.1. EOT procedures should be performed at the point when the decision to discontinue the treatment has been made. A Safety Follow-up Visit should be performed 8 weeks ( $\pm 7$  days) after their last dose of study treatment.

In addition to the EOT Visit, participants who decide to discontinue the treatment in Part A should continue to attend all future scheduled visits through Week 12 for safety and efficacy assessments. A separate Safety Follow-up Visit is not required if the participant attends a scheduled visit at 8 weeks after treatment discontinuation.

If the patient discontinues treatment in Part B, EOT procedures should be performed at the point when the decision to discontinue the treatment has been made. A Safety Follow-up Visit should be performed 8 weeks ( $\pm 7$  days) after their last dose of study treatment.

In case the participant does not agree to continue with all scheduled visits, the participant will be withdrawn from the study.

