| BASDAI                                              |                   | X      |    | X  |    | X  |    | X               |    | X      |     | X   |     | X                   |                         |                  |
|                                                     |                   |        |    |    |    |    |    |                 |    |        |     |     |     |                     |                         |                  |
| TJC68 and SJC66 h                        | X                 | X      | X  | X  |    | X  |    | X h  | X  | X      |     | X   |     | X                   |                         |                  |
| PhGADA                                              |                   | X      | X  | X  |    | X  |    | X               | X  | X      |     | X   |     | X                   |                         |                  |
| BSA affected by PsO (BSA palm method)               |                   | X      |    |    |    |    |    | X               |    |        |     |     |     | X                   |                         |                  |
| PASI                                                |                   | X      |    | X  |    | X  |    | X               |    | X      |     | X   |     | X                   |                         |                  |
| LDI                                                 |                   | X      |    | X  |    | X  |    | X               |    | X      |     | X   |     | X                   |                         |                  |
| Enthesitis evaluation (LEI+SPARCC enthesitis index) |                   | X      |    | X  |    | X  |    | X               |    | X      |     | X   |     | X                   |                         |                  |
| mnAPSI                                              |                   | X      |    |    |    |    |    | X               |    |        |     |     |     | X                   |                         |                  |
| 12-lead ECG                                         | X                 |        |    |    |    |    |    | X               |    |        |     |     |     |                     | X                       |                  |
| Height                                              | X                 |        |    |    |    |    |    |                 |    |        |     |     |     |                     |                         |                  |

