#### 7.2.1.2 Sensitivity Estimand

The sensitivity estimand will include data from participants in the target population of the primary estimand plus data collected after the withdrawal of study treatment through Week 12 from participants who discontinue study treatments prior to Week 12 for reasons other than lack of efficacy or response.

The attributes of the sensitivity estimand of the primary endpoint are as follows:

- Target population: adults with a confirmed diagnosis of PsA per the 2006 CASPAR [Taylor W. et al., 2006] with symptoms for  $\geq 6$  months prior to the Screening Visit;
- Treatment: sonelokimab at 3 different regimens: sonelokimab 120 mg Q2W, sonelokimab 60 mg Q2W, or sonelokimab 60 mg Q4W;
- Primary endpoint: is percentage of participants achieving ACR50, i.e., at least 50% improvement in the ACR response criteria at Week 12 compared with baseline;
- Intercurrent events: intercurrent events include the following:
  - Use of prohibited concomitant medication (Section 10.5): participants will be analyzed as a treatment failure after taking prohibited medication, i.e., non-responder imputation will be performed after the first episode of prohibited medication for all future assessments (composite strategy);
  - Withdrawal from treatment due to lack of efficacy (Section 9.6): participants will be considered non-responders to treatment if they discontinue the study prior to the Week 12 Visit (composite strategy);

- Withdrawal from treatment due to any reason other than lack of efficacy (Section 9.6): participants will continue to be followed and use their observed Week 12 Visit (treatment policy strategy). Any missing data for participants who do not have a Week 12 visit will be assumed to be missing at random;
- Study treatment non-adherence (missing doses) or drug administration error: participants will be analyzed the same if the event occurs or not (treatment policy strategy).

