#### **9.6.2 Non-Compliance**

Participants will be deemed non-compliant if they significantly violate protocol requirements or in the event that 2 doses are missed in either Part A or Part B, or 2 consecutive visits are missed.

The EOT Visit and the Safety Follow-up Visit, as described in the SOA in Section 3, Table 1, will be conducted in all withdrawn participants willing to undergo the assessments. The EOT Visit will occur as soon as possible after study treatment withdrawal, while the Safety Follow-up Visit will occur 8 weeks ( $\pm 7$  days) after the administration of the last dose of study treatment.

The investigator must also contact the IRT to register the participant's discontinuation from study treatment.

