#### **11.3.2 Time Period and Frequency for Collecting Adverse Events and Serious Adverse Events Information**

For the purposes of this study, any detrimental change in the participant's condition after signing the ICF and up to completion of the Safety Follow-up Visit (or until withdrawal from the study, whichever is later) will be considered an AE. AEs will be collected at every study visit (Section [3](#), [Table 1](#)). Any relevant observations made prior to the first dose of study treatment are to be

recorded on the AE eCRF but will not be considered TEAEs and will be reported separately from TEAEs.

At any time after completion of the Safety Follow-up, if an investigator learns of an SAE that can be reasonably related to study treatment, they will promptly notify the sponsor.

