| Endpoint                                           | 
 
– Percentage of participants achieving ACR50, i.e., at least 50% improvement in the ACR response criteria at Week 12 compared with baseline.
 
                                                                                                                                                                                                                                                                                                                                                                                                                                                                                                                                                                                                                                                               |
| Intercurrent events and strategies to handle those | 
 
• Use of prohibited concomitant medication (Section 10.5.1 of protocol): observed data after taking prohibited medication will be used in the analysis (treatment policy strategy); Any missing data for participants who do not have a Week 12 visit will be assumed to be missing at random;
 
• Withdrawal from treatment for any reason (Section 9.6 of protocol): participants will continue to be followed and use their observed Week 12 Visit (treatment policy strategy). Any missing data for participants who do not have a Week 12 visit will be assumed to be missing at random;
 
• Study treatment non-adherence (missing doses) or drug administration error: participants will be analyzed in the same way as if the event had occurred or not (treatment policy strategy).
 
 |

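### Protocol 9.4 withdraws Part A discontinuers who will not agree to every remaining visit, so some Week 12 outcomes that the treatment-policy sensitivity estimands call for may never be observed

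*Combined protocol and SAP*

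**What the plan says.** Protocol 9.4 separates stopping treatment from leaving the study. In addition to an End-of-Treatment (EOT) visit, "participants who decide to discontinue the treatment in Part A should continue to attend all future scheduled visits through Week 12". Protocol 8.3.5 repeats this. The section then closes with an all-or-nothing condition: "In case the participant does not agree to continue with all scheduled visits, the participant will be withdrawn from the study". It offers no reduced schedule and no Week 12-only option.

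Protocol 9.6.1 reserves withdrawal of consent for someone who wants no further visits, assessments or study contact. Protocol 9.6.2, on non-compliance, provides an EOT visit and a Safety Follow-up Visit that "will be conducted in all withdrawn participants willing to undergo the assessments"; it does not mention Week 12.

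The sensitivity estimands assume continued follow-up. In SAP 5.2 the second one reads: "Withdrawal from treatment for any reason (Section 9.6 of protocol): participants will continue to be followed and use their observed Week 12 Visit". Protocol 7.2.1.2 says the same for withdrawal for reasons other than lack of efficacy. The first estimand in SAP 5.2 says it for reasons other than lack of efficacy or an adverse event. In each case a missing Week 12 value is assumed missing at random.

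**The concern.** The primary analysis counts early stoppers as failures. The treatment-policy sensitivity estimands exist to show whether the result depends on that choice, and for this they need real Week 12 outcomes from people no longer on drug. Under 9.4, a participant who declines an intermediate visit is withdrawn even if willing to come at Week 12. The outcome that the estimand is defined on is then replaced by an imputed value. The more often this happens, the more these analyses reflect the missing-at-random assumption rather than what was observed off treatment.

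**Working it through.** **1. Which visits the rule covers.** In the Schedule of Activities (protocol section 3), the rows for TJC68/SJC66, PtGADA, PtAAP, HAQ-DI, PhGADA and hs-CRP are marked at Weeks 0, 2, 4, 8 and 12 in Part A. None is marked at Week 6 or Week 10. Those two visits carry adverse-event evaluation, concomitant medication review, vital signs and dosing; protocol 11.3.2 confirms that "AEs will be collected at every study visit". They have a safety purpose but add nothing to ACR50.

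**2. Whether 9.4 is stricter than withdrawal of consent.** Under 9.6.1, a person willing to attend Week 12 has not withdrawn consent. Under the last sentence of 9.4, the same person is withdrawn for not agreeing to all visits.

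**3. Whether another visit supplies the Week 12 value.**
- *EOT visit.* It includes every ACR component, and SAP 7.2 lets a discontinuation assessment fill a visit window. The Week 12 window for these components is Day 72 to 92. Because EOT is done when the decision to stop is made, a stop before Day 72 falls in an earlier window.
- *Safety Follow-up Visit.* It has no joint counts in the schedule, so it cannot yield ACR50 even when its date falls within Day 72 to 92.

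**4. Which estimands need the value.**

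| Estimand | Withdrawals for which Week 12 is to be observed |
|---|---|
| Protocol 7.2.1.2 | All reasons except lack of efficacy |
| SAP 5.2, first | All reasons except lack of efficacy or adverse event |
| SAP 5.2, second | All reasons |

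The second SAP estimand is the most exposed. Protocol 7.2.2.2 and SAP 5.4 repeat the structure for the key secondary endpoints.

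**5. Size.** The plan gives no discontinuation rate; SAP 5.5 says no allowance for dropout is needed. Its only related figure is the power statement, reproduced here to confirm the inputs. With 40 per arm, 40% against 10% and two-sided alpha 0.025 (z = 2.241):

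(0.30 − 2.241 × √(2 × 0.25 × 0.75/40)) / √((0.10 × 0.90 + 0.40 × 0.60)/40) = 0.0830/0.0908 = 0.914, which gives power of 82.0%. This agrees with the stated figure of more than 80%.

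One unobserved outcome moves an arm's rate by at most 1/40 = 2.5 percentage points.

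For scale, *assume* m participants per arm have no Week 12 value and the other 40 − m respond at the design rates. The extreme bounds on the 30-point difference are:
- lower: [0.40(40 − m) − (0.10(40 − m) + m)]/40
- upper: [(0.40(40 − m) + m) − 0.10(40 − m)]/40

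| m per arm (of 40) | Lower (points) | Upper (points) |
|---|---|---|
| 1 (2.5%) | 26.8 | 31.8 |
| 2 (5%) | 23.5 | 33.5 |
| 4 (10%) | 17.0 | 37.0 |

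The width is 2m/40, or 5 points for each participant missing in both arms. The values of m are illustrations, not estimates.

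**The case against.** The best defence is that the main safeguard is already written. Sections 9.4 and 8.3.5 ask Part A discontinuers to attend through Week 12 for safety and efficacy, so the closing sentence affects only a person who refuses some visits and would still attend Week 12. The plan also prespecifies imputation of ACR components from earlier visits (SAP 8.6.1.3) and an observed-data analysis, and it labels all sensitivity analyses exploratory. All of this stands, and it limits the size of the point. It does not remove the conflict, because for that subset the protocol ends follow-up that the estimand says continues.

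Several stronger readings are tempting, but the documents do not support them:

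- *Weeks 6 and 10 are dosing-only visits.* They include scheduled safety checks.
- *Missing one visit triggers withdrawal.* The trigger is not agreeing to continue with all visits. Under protocol 8.6, a visit that cannot take place is skipped and the participant goes on to the next one.
- *Participants stopped by the investigator, or withdrawn for non-compliance, are excluded from Week 12.* The wording about participants who decide to stop, and the silence of 9.6.2, are ambiguous rather than a stated exclusion. The second paragraph of 9.4 builds on the first, which covers investigator-led stops, and the third gives the Part B contrast. The text can therefore be read as separating Part A from Part B.
- *Loss will differ by arm.* Nothing in the documents says who initiates which kind of stop in which arm.
- *The primary result is affected.* Protocol 7.2.1.1 counts stopping treatment before Week 12 as failure, so that estimand needs no Week 12 value. The non-responder rules in protocol 12.3.2.1 and SAP 7.3.1 are worded around leaving the study, which is a separate drafting question on which this point does not rest.

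**Conclusion.** The point holds as a limited inconsistency between the follow-up rule and the estimands. As written, 9.4 can remove a consenting participant before a Week 12 assessment that protocol 7.2.1.2 and SAP 5.2 intend to observe. The EOT visit recovers the value only for stops within Day 72 to 92.

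A reader might infer that Week 12 data are lost for discontinuers in general. That goes too far: those who agree to the visits are followed, and the first SAP estimand needs no Week 12 value after withdrawal for lack of efficacy or an adverse event. The number affected is unknown, and each case is worth up to 2.5 points in one arm of an exploratory analysis.

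The conclusion assumes that the closing sentence of 9.4 applies to Part A. It follows the Part B paragraph and names no part, but continued visits after stopping are required only in Part A. It also rests on the section text, because the schedule's footnotes, including the one on the Week 24/EOT column, are not in the text available for review.

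**What to change.** Replace the last sentence of protocol 9.4 with wording such as: *A participant who stops treatment in Part A and is unwilling to attend every remaining visit will be asked to attend at least the Week 12 efficacy assessment, in addition to the required safety follow-up, and will not be withdrawn from the study solely for declining intermediate visits.*

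In 9.4 and 8.3.5, state that follow-up through Week 12 applies to every Part A treatment discontinuation, whoever initiates it. Reconcile 9.6.2 with this. Leave the other grounds for study withdrawal unchanged.

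The change is to wording only, and the Week 12 visit is already in the schedule. For a participant whose last dose was at Week 4, the safety follow-up is due on the same day (Day 29 + 56 = Day 85). The cost is that some participants will have partial off-treatment attendance, with fewer intermediate visits, and so fewer scheduled safety checks, than the full schedule provides.
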